**Fig. 1 Fig1:**
[figure not shown]
SPIRIT figure illustrating the study schedule

### Sample size prediction/statistics

It has been shown that the annual event rate for the defined primary endpoint is 6.3% in case of a pathological and 1.0% in case of a normal CMR examination [27]. Retrospective analysis of our data revealed a 30% rate of pathological CMR examinations during the last years, thus the expected annual event rate would be 2.59% for the whole primary CMR group. In patients primarily undergoing coronary angiography, pooled annual event rates have been shown to be about 6% [6, 28]. For the sample size prediction, a Fisher’s exact test with a power of 80% and a *p* value indicating significance of < .05 was used. The study was designed to prove non-inferiority with a defined non-inferiority margin of 1% within a 3-year follow-up period. This lead to a predicted sample size of 90 participants per group. Taking dropout rate and safety margin into account, we plan to enroll 100 patients into each group. Annual interim analyses will be performed to evaluate the need for further enrollment in case of insufficient event rates for an appropriate statistical analysis.

The following statistical tests will be used after completion of follow-up: to test the relationship between categorical classification factors, the chi-squared test will be applied. Continuous variables will be tested for normal distribution by the D’Agostino-Pearson test. In case of a normal distribution, variables will be reported as mean ± standard deviation and a two-tailed *t* test will be applied for comparison. Variables without normal distribution will be reported as median with percentiles and the Mann-Whitney rank-sum test will be used for comparison. As mentioned above, Fisher’s exact test will be applied to test for non-inferiority of the event rates of both groups. Overall, a *p* value ≤ .05 will be judged significant.

Data management will only be carried out by trained personal. The database is stored on protected servers of the academic hospital.

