## Background

Current guidelines for the diagnosis and management of patients with stable coronary artery disease (CAD) recommend – besides thorough history and physical examination – proper risk stratification and non-invasive detection of myocardial ischemia prior to invasive therapy [1, 2]. The detection or exclusion of moderate to severe reversible myocardial ischemia is a crucial part of the work-up process. When ischemia is present, patients are designated to a high-risk group with a high probability of having a prognostic benefit from revascularization procedures [3–5]. Patients without ischemia do not seem to benefit from revascularization over optimal medical therapy, at least with regard to prognosis [6]. This emphasizes the need for functional testing prior to therapeutic decisions.

Adenosine perfusion cardiac magnetic resonance imaging (CMR) is an imaging modality which is able to reliably detect reversible myocardial ischemia and thus plays an increasing role in the diagnosis and risk stratification of patients with suspected or known CAD [7–11]. Though CMR, therefore, is highly recommended in the diagnostic work-up of stable CAD patients, there is only one study evaluating a CMR-driven approach in patient management with regard to the occurrence of major cardiac events [12].

Invasive coronary angiography still is considered to be the “gold-standard” for the diagnosis of CAD, though it exhibits several limitations and shortcomings. Multiple studies have documented the significant interobserver variability in the grading of coronary artery stenosis, as well as the frequent occurrence of under- and overestimation of hemodynamic relevance [13, 14]. One has to conclude that coronary angiography may provide anatomical information but is not the modality of choice concerning the detection of myocardial ischemia. This is of special interest, as there is a reported frequency of complications due to diagnostic coronary angiographies of about 1.5% [15]. Nevertheless, coronary angiography remains the most often performed diagnostic test in the setting of stable CAD, with more than one half of elective percutaneous coronary interventions (PCI) done without previous stress testing [16].

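### The stated 80% power for non-inferiority rests on an unexplained 2.3-fold lower event rate under CMR; it is not reached at the 1-point margin even if that benefit is granted, and at equal true rates power is about 4-8% (8-21% with a 3-point margin)

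*Protocol article*

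**What the plan says.** All inputs stand in the protocol article under Sample size prediction/statistics.

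- **CMR arm.** One cited source supplies annual event rates of "6.3% in case of a pathological and 1.0% in case of a normal CMR examination". The weighting comes from the centre: "Retrospective analysis of our data revealed a 30% rate of pathological CMR examinations". The result is given as "thus the expected annual event rate would be 2.59% for the whole primary CMR group".
- **Angiography arm.** "In patients primarily undergoing coronary angiography, pooled annual event rates have been shown to be about 6" (per cent), with two other citations.
- **Test and error rates.** The calculation used "a Fisher’s exact test with a power of 80" (per cent) and a p "value indicating significance of < .05 was used". Whether this is one-sided or two-sided is not said.
- **Margin and size.** The margin is 1% within the 3-year follow-up. The size is 90 per group, raised to 100 for dropout and safety.
- **Analysis.** "Fisher’s exact test will be applied to test for non-inferiority of the event rates of both groups".

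The last paragraph of the Background gives the aim: CMR-based management should be not inferior, and angiographies and PCI could be saved with no loss of safety or comfort. It does not claim that CMR lowers the rate of cardiac death or infarction.

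**The concern.** The two arms are randomised from one clinic population, so their expected share of ischaemic patients is the same. The calculation nevertheless gives them annual rates that differ by a factor of 6/2.59 = 2.3, taken from different cited sources, and offers no reason for the gap. A gap of that size drives the sample size: a trial that would need thousands per arm if the strategies perform alike appears to need 90.

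At stake is the primary claim. If CMR is simply as safe as angiography, which would fully meet the stated aim, the trial will very probably fail to show non-inferiority while being presented as having 80% power. A non-significant comparison could then be misread as evidence of non-inferiority.

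**Working it through.** **1. The plan's own CMR rate.** 0.30 × 6.3% + 0.70 × 1.0% = 1.89% + 0.70% = 2.59% per year. This reproduces.

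**2. Three-year risks (annual rates compounded).**
- CMR: 1 − (1 − 0.0259)³ = 7.57%
- Angiography: 1 − (1 − 0.06)³ = 16.94%
- Presumed advantage: 16.94 − 7.57 = 9.4 points

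**3. What the 6% implies.** Assume, as the article does not say, that 30% ischaemic at 6.3% per year also holds in the angiography arm. The remaining 70% must then have (6 − 1.89)/0.70 = 5.87% per year, against the 1.0% used for a normal CMR in the other arm.

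**4. Does 80% at 90 per group follow if the benefit is granted?** Power = Φ[(Δ + m)/SE − z], where Δ is the CMR advantage, m the margin and SE = √{[p₁(1 − p₁) + p₂(1 − p₂)]/n}. With p₁ = 0.0757 and p₂ = 0.1694, SE is 0.0484 at n = 90 and 0.0459 at n = 100. For example, at n = 90, m = 0.01 and one-sided 5%: (0.0937 + 0.01)/0.0484 − 1.645 = 0.50, so power is 69%. Exact binomial enumeration of the same confidence-interval rule is in brackets.

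| n per group | margin | one-sided 2.5% | one-sided 5% |
|---|---|---|---|
| 90 | 1 point | 57% (59%) | 69% (71%) |
| 100 | 1 point | 62% (63%) | 73% (74%) |
| 90 | 3 points | 72% (74%) | 82% (83%) |

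The 3-point row reads the margin as 1% per year. At n = 90, only that reading together with one-sided 5% gives about 80%. For the literal margin the formula needs 122 per group (one-sided 5%) or 154 (one-sided 2.5%). Tripling the annual rates, or using exponential risks, moves power at n = 90 and 1 point only within 55-74%. Fisher's exact test with the control rate shifted by 1 point is less favourable still: 60% at n = 90, one-sided 5%.

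**5. Power at equal true rates, 100 per group.** Now Δ = 0.

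| Common annual rate (3-year risk) | margin | one-sided 2.5% | one-sided 5% |
|---|---|---|---|
| 2.59% (7.57%) | 1 point | 4.5% (4.4%) | 8.4% (8.5%) |
| 6% (16.94%) | 1 point | 3.8% (4.0%) | 7.3% (7.5%) |
| 2.59% (7.57%) | 3 points | 12.3% (12.7%) | 20.0% (20.6%) |
| 6% (16.94%) | 3 points | 8.2% (8.6%) | 14.0% (14.5%) |

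**6. The same fact as precision.** At a common 7.57%, SE = √(2 × 0.0757 × 0.9243/100) = 0.0374, so the 95% interval has a half-width of 1.96 × 3.74 = 7.3 points. CMR would have to be observed at least 7.3 − 1 = 6.3 points better to exclude a 1-point margin.

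**7. Scale of the gap.** For 80% power at equal rates and a 1-point margin, the formula needs about 8,650 to 17,400 per group (one-sided 5%) or 10,985 to 22,089 (one-sided 2.5%). For 3 points it needs about 960 to 2,455 across both levels.

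**The case against.** Powering a non-inferiority trial on an expected benefit is a legitimate choice, and the article says not inferior, not equivalent. This stands: the assumption is not wrong in kind. What remains is that the benefit is large, unexplained and decisive for the size.

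Several stronger readings are tempting and go beyond the text:

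- *The Background contradicts the assumption.* It says "Patients without ischemia do not seem to benefit from revascularization over optimal medical therapy, at least with regard to prognosis". That speaks of absent benefit, with a hedge; it does not say that prognosis is the same, and it does not exclude harm from unnecessary procedures. The article even names a direction for such harm, with about 1.5% complications of diagnostic angiography, although that falls far short of 9.4 points.
- *The two rates come from different populations.* The article shows different citations but does not describe those cohorts. This is an inference, as is the 5.87% in step 3.
- *The 80% is at least correct, given a 9.4-point advantage.* Step 4 shows that at the literal margin it is not.

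One may also object that enrolment is not fixed, because annual interim analyses can extend it. That rule responds to low event rates, not to the assumed difference. With 6% per year in both arms, power at the 1-point margin is still no more than about 8%.

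Finally, the power figures use a risk-difference interval and not the Fisher test that the plan names. An ordinary Fisher test of equal rates contains no margin, so some substitute is needed; the shifted Fisher version gives lower power, so the choice does not work against the plan.

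**Conclusion.** The point holds. The stated 80% is a figure that the design does not deliver under the margin as written: power is about 57-71% at 90 and 62-74% at 100 per group with the presumed 9.4-point advantage granted. It is about 4-8% at 100 per group if the arms have equal true rates. Reading the margin as 1% per year raises the equal-rate power to 8-21% and leaves the conclusion unchanged.

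These figures assume compounded 3-year risks, complete follow-up, a risk-difference test, one-sided levels of 2.5% and 5% because the sidedness is not stated, and common rates between 2.59% and 6% per year. They do not depend on where the cited rates came from. The verdict is not that the Background refutes the assumed benefit, nor that planning on a benefit is improper; the documents support neither.

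**What to change.** Revise the sample-size paragraph, without increasing enrolment:

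1. State that the size presumes a CMR advantage of about 9.4 points at 3 years (2.59% against 6% per year), and give the reason for expecting it or say that there is none beyond the cited rates.
2. State whether the test is one-sided at 5% or at 2.5%, and whether the margin is 1 point over 3 years or 1 point per year.
3. Replace the 80% with the power obtained under that assumption, and add the power at common rates of 2.59% and 6% per year. It should not be written that 80% holds given the 9.4-point advantage, because at the 1-point margin that is untrue.
4. Conclude non-inferiority only if the confidence interval for the risk difference, at the level matching item 2, excludes the margin. Otherwise report the estimate with its interval as inconclusive, and not as no difference.

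The cost is wording in the protocol and analysis plan, and a much less favourable stated power. The change makes the claim honest; it does not make the trial able to show non-inferiority if the strategies perform alike.

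### The 90 per group does not follow from the stated rates, 1% three-year margin and 80% power; those inputs need about 108–163 per group, and 90 gives roughly 55–74% power

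*Protocol article*

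**What the plan says.** Everything sits in one paragraph of the protocol article, Sample size prediction/statistics.

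- CMR arm: annual rates of "6.3% in case of a pathological and 1.0% in case of a normal CMR examination", combined with "a 30% rate of pathological CMR examinations during the last years", so that "the expected annual event rate would be 2.59% for the whole primary CMR group".
- Angiography arm: "pooled annual event rates have been shown to be about 6" per cent.
- Test and power: Fisher's "exact test with a power of 80" per cent, with a p "value indicating significance of < .05 was used". Sidedness is not given.
- Margin: "The study was designed to prove non-inferiority with a defined non-inferiority margin of 1% within a 3-year follow-up period".
- Result: "This lead to a predicted sample size of 90 participants per group", raised to 100 per group for dropout and a safety margin. No dropout rate is given.

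The same section names Fisher's exact test again for the final non-inferiority comparison. The Protocol section fixes 1:1 allocation, and the Follow-up section fixes 3 years per patient.

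**The concern.** The event rates are annual, while the margin is tied to 3 years. The paragraph does not say how one was carried to the other, and the resulting number looks too small for a 1-point margin. The margin is the criterion by which the CMR strategy will be declared non-inferior on cardiac death and non-fatal myocardial infarction, and the power is the stated chance of showing it. If the printed inputs and the printed sample size do not belong together, a reader cannot tell which of them is wrong. Under the plan's own assumptions, the risk of an inconclusive trial is then larger than the 20% stated. The annual reviews of whether to enrol more patients would also start from an incorrect power figure.

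**Working it through.** **The plan's own figures.** The CMR rate reproduces: 0.30 × 6.3% + 0.70 × 1.0% = 2.59% per year. The 90 per group does not.

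**Assumptions where the text is silent.** The margin is taken as an absolute difference. Alpha is tried at one-sided 5% and at one-sided 2.5% (the two-sided 5% equivalent). Annual rates r are converted to 3-year risks in three ways:

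| Conversion | CMR risk p_t | Angiography risk p_c | Difference |
|---|---|---|---|
| Linear, 3r | 7.77% | 18.00% | 10.23 points |
| Compounded, 1 − (1 − r)³ | 7.57% | 16.94% | 9.37 points |
| Exponential, 1 − exp(−3r) | 7.48% | 16.47% | 9.00 points |

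**Sample size for 80% power.** The formula is n = (z_α + z_β)² [p_c(1 − p_c) + p_t(1 − p_t)] / (p_c − p_t + m)², with m = 0.01.

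Compounded risks, one-sided 5%: (1.645 + 0.842)² = 6.18; variance term 0.1407 + 0.0700 = 0.2107; denominator (0.0937 + 0.01)² = 0.01076. So n = 6.18 × 0.2107 / 0.01076 ≈ 121.1, rounded up to 122.

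**Power at a given n.** Power = Φ{(p_c − p_t + m) √(n / variance term) − z_α}. For the same case at n = 90: 0.1037 × √(90 / 0.2107) − 1.645 ≈ 0.499, and Φ(0.499) ≈ 69%.

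| Conversion | Alpha (one-sided) | n per group for 80% | Power at 90 | Power at 100, no dropout |
|---|---|---|---|---|
| Linear | 5% | 108 | 74% | 77% |
| Compounded | 5% | 122 | 69% | 73% |
| Exponential | 5% | 128 | 67% | 71% |
| Linear | 2.5% | 137 | 62% | 67% |
| Compounded | 2.5% | 154 | 57% | 62% |
| Exponential | 2.5% | 163 | 55% | 59% |

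The Farrington-Manning restricted variance gives 111–167 per group. Using the annual rates directly with a 1-point margin gives 260 per group at one-sided 5%. None of these is 90.

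**The named test.** Fisher's exact test as named tests equality, with no margin. Power at 90 per group, by full enumeration of the two binomials (linear / compounded / exponential):

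- One-sided 5%: 59% / 53% / 50–51%.
- Two-sided 5%: 47% / 41% / 39%.
- Rates shifted by 1 point to mimic the margin: 46–65% if the point is added to the angiography risk, and 49–68% if it is taken off the CMR risk, over both alphas and all three conversions.

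Without a margin, Fisher's test would need about 146–178 per group (one-sided 5%) or 184–218 (two-sided 5%).

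**Where values near 90 do arise.** With m = 0.03 and one-sided 5%, the first formula gives 78 (linear), 86 (compounded) or 89 (exponential), and Farrington-Manning with compounded risks gives 89. A Poisson person-time formula with 1% per year gives 91. A two-sided 5% comparison on linear risks, with the CMR risk lowered by 3 points, gives 90. All of these use 3 points over 3 years, or 1% per year.

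**The case against.** The best defence is that 90 can be approached. If the 1% is read as annual, several standard formulas land close to it. The article also condenses a fuller protocol that may hold the actual calculation. It plans 100 per group rather than 90, and it foresees annual reviews of whether more patients are needed if events are too few.

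This only partly helps. The text attaches the 1% to the 3-year period and names a test that none of those formulas uses. This is also not a detail left to another document: rates, power, alpha, margin, time frame and result are all printed and do not agree. Enrolling 100 with no dropout gives at most 77%, and the enrolment review is triggered by event rates, not by the margin.

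The objection does stand against several stronger readings that a reader might infer:

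- *The trial was really sized for 3 points, or annual and 3-year scales were mixed.* This is back-solved from the answer. Nothing in the article mentions a 3-point margin, so it is one possible explanation and no more.
- *Only a one-sided 5% test with 3 points recovers 90.* The two-sided shifted-rate calculation reaches it too, so the recipe used cannot be identified.
- *Power with Fisher's test against the 1-point margin is as low as 39–59%.* That range belongs to a test of equality with no margin. With the margin built in by shifting the rates, it is about 46–68%.

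**Conclusion.** The point holds as a failure to reproduce: 90 per group and 80% power are not consistent with the printed rates and a margin of 1 point over 3 years. The required size is 108–128 (one-sided 5%) or 137–163 (one-sided 2.5%) evaluable patients per group. Power at 90 is 67–74% or 55–62%, and at 100 with no dropout it is 59–77% across both alphas. Fisher's test stays below 80% with or without the 1-point shift.

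These figures rest on an absolute margin, complete 3-year follow-up, and the plan's favourable expectation that CMR patients have fewer than half the events of the angiography group. The ranges cover the unstated sidedness and rate conversion, and no combination tried with the written margin rescues 90. What the documents do not show is how 90 was obtained, or that a margin other than 1 point was intended.

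**What to change.** Correct the paragraph; enrolment need not change.

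1. State the 3-year risks actually used for each arm and how they were derived from the annual rates. The conversions above are illustrations and should not be adopted as if they were the original inputs.
2. Name a test that incorporates the margin, and use it for the analysis as well as for the sample size.
3. State alpha and whether it is one- or two-sided.
4. State the margin as an absolute difference on the 3-year scale.
5. Replace 80% with the power achieved for the 1-point margin. With 90 evaluable per group this is about 67–74% at one-sided 5% or 55–62% at one-sided 2.5%, to be narrowed once items 1–3 are fixed.

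The margin should be restated as 3 points only if the original pre-recruitment calculation documents that this was the design, and then as a recorded protocol modification through the ethics committee and registry route that the article describes. That it fits the sample size is not a reason to widen it, particularly as recruitment was ongoing at submission.

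The cost is rewording, retrieval of the original calculation, and a less favourable stated power.

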The objective of our study is to show that a CMR-based conservative or invasive management of patients with suspected or known CAD is not inferior with regard to major cardiac endpoints and quality of life in comparison to a – more conventional – coronary angiography-based approach. We assume that a significant number of diagnostic coronary angiographies and PCI could be spared without decrease in patient safety and comfort. Therefore, we designed this single-center, open-label, randomized controlled trial to test for non-inferiority of the two diagnostic groups.

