### Protocol

All patients receive thorough history-taking, physical examination and a basic cardiological work-up including rest electrocardiogram, treadmill testing and echocardiography. Further prediagnostics (e.g., stress-echocardiography) is allowed and the respective results will be documented. According to general recommendations, risk stratification scores for each individual are calculated [18, 19]. In order to assess symptom burden and quality of life, the standardized Seattle Angina Questionnaire (SAQ) is carried out in each subject [20, 21]. All patients receive guideline-directed medical therapy (GDMT) [1].

Patients are randomized in two groups in a 1:1 fashion (blocked computer-generated random numbers). The allocation sequence is only available to a designated study nurse who will be phoned in case of an allocation. The trial is designed in an open-label fashion, i.e., there is no blinding after the initial allocation.

In group 1, patients directly undergo diagnostic coronary angiography. A PCI is performed according to current guidelines in case of ≥70% stenosis in a coronary vessel with ≥2-mm diameter [1, 2] or hemodynamically relevant stenoses in fractional flow reserve (FFR) testing.

Subjects in group 2 initially receive adenosine perfusion CMR for functional testing. The examination is conducted on a 3.0-Tesla whole-body scanner with a 32-channel phased-array cardiac receiver coil according to a well-established standard protocol [22–24]. In case reversible ischemia can be detected, subjects are sent to coronary angiography and PCI afterwards. Additional file 5: Figure S1 provides the study flowchart.

In case of progressive or insufficient symptom control, patients of group 2 (CMR group) are also evaluated for an invasive therapeutic approach. The following procedures will be documented.

There are no other diagnostic or therapeutic interventions planned or prohibited in the setting of this trial.

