### Follow-up

Adherence will be achieved by regular contact between the study personal and the participants. Follow-up information is gathered on a yearly basis after enrollment by outpatient clinic visits and by telephone interviews of patients and their general practitioners. Any reported adverse event will be reported and its significance evaluated by the investigators. At this time point, interim analyses will be performed by the investigators. The study will be stopped by the investigators if a safety concern arises that prohibits the continuation of the trial.

The primary endpoint is defined as cardiac death (defined as in [25]) and non-fatal myocardial infarction according to the current universal definition [26]. Any diagnostic or interventional coronary procedure that has not been scheduled at the time of the initial diagnostic work-up will be recorded as an unplanned procedure. Symptom burden and quality of life are assessed by SAQ each year. A follow-up period of 3 years is planned for each patient. Standardized follow-up forms have been established and are available at our institution. If consent is withdrawn by a participant, the data that has already been collected will be removed from further analysis.

Figure 1 shows the study schedule according to the populated SPIRIT figure.

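### The only stated rule for continuous outcomes, which by inference covers the SAQ, is an unadjusted test chosen by a normality pre-test; adjusting for the baseline SAQ would add precision from data already collected

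*Protocol article*

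**What the plan says.** All references are to the Protocol article.

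- **Collection.** The section Protocol states: "In order to assess symptom burden and quality of life, the standardized Seattle Angina Questionnaire (SAQ) is carried out in each subject". This comes in the description of the initial work-up, ahead of the paragraph on randomization. The section Follow-up adds: "Symptom burden and quality of life are assessed by SAQ each year", over three years per patient.
- **Role.** The objective at the end of the Background is that CMR-based management "is not inferior with regard to major cardiac endpoints and quality of life in comparison to a" angiography-based strategy. Quality of life therefore stands beside the cardiac endpoints in the non-inferiority aim.
- **Analysis.** Sample size prediction/statistics lists the tests to be applied once follow-up is complete. For continuous data it says: "Continuous variables will be tested for normal distribution by the D’Agostino-Pearson test". If normality is accepted, "variables will be reported as mean ± standard deviation and a two-tailed" t test follows. Otherwise medians with percentiles are given and "the Mann-Whitney rank-sum test will be used for comparison". A p "value ≤ .05 will be judged significant".

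The analysis text does not name the SAQ, a covariate or a repeated-measures model, and does not say whether scores or changes from baseline are compared.

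**The concern.** A patient's questionnaire score before treatment usually predicts part of the score afterwards. A two-sample test without that covariate leaves predictable between-patient variation in the error term. The trial collects the baseline score anyway, so the information is paid for but not used in the way that gives the most precision.

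The pre-test adds a second difficulty. The choice between mean with t test and median with rank test is made from the outcome data, so the summary measure is not fixed in advance and could differ between SAQ scales or years. If scores pile up at the top of the scale, the rule leads to Mann-Whitney, and the report then holds medians and a p value. A non-inferiority aim for quality of life needs an estimated group difference with a confidence interval.

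**Working it through.** **Inputs.** From the article: 1:1 allocation, 90 patients per group calculated and 100 per group to be enrolled (the excess allows for dropout and safety), significance at 0.05. The article gives no SAQ standard deviation, correlation, target difference or sample size, so there is no SAQ figure of its own to reproduce. The calculated 90 per group belongs to the primary endpoint and is taken as given. Assumed here: a baseline-to-follow-up correlation ρ of 0.3 to 0.7, equal SD at both times and in both arms, and a two-sided test. An SD of 20 points is used only to put one result on the score scale.

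**Step 1: variance factors.** Relative to comparing follow-up scores at one year (factor 1):

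- ANCOVA with baseline as covariate: 1 − ρ²
- change from baseline: 2(1 − ρ)
- ANCOVA relative to change: (1 − ρ²) / [2(1 − ρ)] = (1 + ρ)/2

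Since 2(1 − ρ) − (1 − ρ²) = (1 − ρ)², the change score is less precise than ANCOVA for every ρ below 1.

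| ρ | ANCOVA factor | Cut vs follow-up score | 100 per arm act like | Change factor | ANCOVA / change | Cut vs change |
|---|---|---|---|---|---|---|
| 0.3 | 0.91 | 9% | 100/0.91 = 110 | 1.4 | 0.65 | 35% |
| 0.5 | 0.75 | 25% | 100/0.75 = 133 | 1.0 | 0.75 | 25% |
| 0.7 | 0.51 | 49% | 100/0.51 = 196 | 0.6 | 0.85 | 15% |

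**Step 2: confidence interval.** With SD 20 (assumed) and 100 per arm, the half-width is 1.96 × 20 × √(2/100) = 5.54 points unadjusted, and 5.54 × √0.75 = 4.80 at ρ = 0.5, which is 13% narrower. With 90 per arm it is 1.96 × 20 × √(2/90) = 5.84, falling to 5.84 × √0.75 = 5.06.

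**Step 3: detectable difference and power.** The difference detectable with 80% power is (1.96 + 0.84) × √(2/n) SD, multiplied by √(1 − ρ²) if adjusted. Power is for a true difference of 0.3 SD.

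| n per arm | Quantity | Unadjusted | ρ = 0.3 | ρ = 0.5 | ρ = 0.7 |
|---|---|---|---|---|---|
| 100 | Detectable difference (SD) | 0.396 | 0.378 | 0.343 | 0.283 |
| 100 | Power | 56.4% | 60.4% | 68.8% | 84.4% |
| 90 | Detectable difference (SD) | 0.418 | 0.398 | 0.362 | 0.298 |
| 90 | Power | 52.1% | 55.9% | 64.2% | 80.5% |

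**Step 4: behaviour of the pre-test rule.** A simulation with 5000 runs per setting and 100 per arm applied the rule to follow-up scores, with ρ of 0.3, 0.5 and 0.7:

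- Type I error was 4.8% to 5.4% across settings.
- For a 0.3 SD shift in normal scores, power was 54% to 56% under the rule, against 59%, 69% and 84% for ANCOVA.
- For 0–100 scores with a ceiling, power was 53% under the rule, against 57%, 64% and 79% for ANCOVA.
- Ceiling scores passed the normality test in both arms in only about 1% to 8% of runs, so Mann-Whitney was almost always selected.

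**The case against.** The strongest reply is that the statistics section never mentions the SAQ. It gives a generic rule and does not exclude a comparison of changes. This stands as a limit on the point: applying the rule to the SAQ is an inference. A reader might conclude that the article explicitly plans separate tests of follow-up scores that disregard baseline; the text does not say that. The change-score reading does not remove the loss, however, as step 1 shows.

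A second reply is that covariates for a secondary questionnaire are usually left to a statistical analysis plan, which is not shown. That would answer a complaint about silence. Here the article states which tests will be used for continuous variables, and the criticism is of that stated rule.

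Third, a reader might infer that the missing adjustment biases the result, or that the pre-test inflates false positives. Neither is supported. An unadjusted comparison of randomized groups is unbiased, chance baseline imbalance is already reflected in its standard error, and the simulated error rate stayed near 5%. If scores are as ceiling-limited as supposed, switching between tests would also be uncommon; what remains is mainly the lack of an estimate with an interval.

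Fourth, the size is uncertain. Neither the correlation nor the SD is documented, the gain is small at ρ = 0.3, and it shrinks somewhat with ceiling scores. The narrowing in step 2 is measured against a mean-difference interval that the Mann-Whitney branch would not produce. All this is fair, and the figures are illustrative.

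Finally, adjustment alone does not deliver the quality-of-life non-inferiority aim, because no SAQ margin is stated in the article. That is true and a separate matter; an adjusted difference with its interval is what any margin would be applied to.

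**Conclusion.** The point holds as one of efficiency and of fixing the estimate in advance. The only rule the article gives for continuous outcomes, read as covering the SAQ, makes no use of baseline as a covariate. The loss is 9% to 49% of the variance if follow-up scores are compared, and 35% to 15% if changes are compared, for an assumed ρ of 0.3 to 0.7. The pre-test leaves the summary measure unfixed and, with ceiling-limited scores, would usually end in a rank test without the adjusted mean difference and interval that the stated aim calls for.

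It is tempting to read this as a flaw in the trial's main comparison. It is not: the primary endpoint, its analysis and the planned 100 per group do not depend on the SAQ. The change is worth making because it is cheap and the SAQ is part of the objective, not because the validity of the trial is in doubt.

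**What to change.** For the SAQ, replace the pre-test rule with a pre-specified model, for example: SAQ scores at years 1 to 3 are analysed in a mixed model for repeated measures with group, year, group-by-year and baseline SAQ score; the adjusted mean difference at 3 years with its 95% CI is reported for each scale. An ANCOVA at 3 years with baseline as covariate is a simpler alternative. Drop the normality test for the SAQ and keep Mann-Whitney as a sensitivity analysis.

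The cost is wording only. No further patients, visits or data are needed, since "the standardized Seattle Angina Questionnaire (SAQ) is carried out in each subject" already. The article reports recruitment as ongoing, so the wording could be fixed before the analysis at completion of follow-up.
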